#### Phase 3 Protocol

##### Baseline (T0)

###### Baseline Interview

Before beginning the VR-ET intervention, participants will have a one-on-one interview with an ETS over a telephone or video call. In this interview, the ETS will explain the 3 sets of scenes that were recorded in phase 2. Then, through discussion, the ETS and participant will determine which exposure set fits best with their individual epilepsy-related fears.

After choosing the appropriate exposure set, the ETS and participant will discuss the most appropriate order in which the 3 scenes associated with the set should be delivered during the intervention. As ET is typically delivered in a hierarchical manner, participants will be exposed to the scenes in the order of least anxiety provoking to most anxiety provoking. The order of exposure scene delivery will be individualized for each participant based on their unique experiences and fears. For example, the exposure set that fits best with 2 participants (hereinafter referred to as participants A and B) may be a shopping mall with its associated social aspects. In this case, the 3 levels may be scenes of a shopping mall with crowds of different sizes (eg, scenes with 2, 10, and 30 people). Participant A may have a fear of not being around many people in a public setting, such as a shopping mall, because it could mean that less help would be available in case they were to get a seizure. Therefore, participant A would first be exposed to the mall scene with 30 people, then 10 people, and then finally 2 people. In contrast, participant B may have a fear of being around many people in a public setting because they worry that having a seizure is embarrassing and would prefer to be surrounded by fewer people if they were to have a seizure [1]. Thus, the ETS would decide with participant B that they should first be exposed to the mall scene with 2 people, then 10 people, and finally 30 people. In summary, opportunities for tailoring the therapy will be built into the intervention through the (1) selection of scenario (location or theme), (2) selection of scenes (based on specific fears within a location such as the number of people in the scene), and (3) ordering of the scenes.

The aim of ET is to expose individuals to their fears until they habituate to the anxiety and learn to predict the outcome of their feared event as less anxiety provoking than they anticipated. Therefore, it is expected that participants may experience anxiety in anticipation of the exposure, during the exposure, and for a short period after completing the exposure. Although ET typically involves letting anxiety subside without instituting coping mechanisms, special considerations must be taken when working with the epilepsy population. Specifically, stress is a commonly self-reported seizure trigger for some people with epilepsy [38]. Although people with epilepsy for whom stress is a known or suspected seizure trigger will be excluded from phase 3, there is still a risk that stress may provoke a seizure in participants. To help prevent this, a number of protocols will be set in place (Textbox 2).

Protocols put in place in case participants become too anxious before, during, or soon after the exposure sessions.
**Coping mechanisms**
Before the baseline interview, participants will be sent a document that provides anxiety coping mechanisms, namely a mindfulness strategy, a self-compassion strategy, and a meditative technique. Participants will be encouraged to practice these coping mechanisms before the interview as they will then review them with the exposure therapy specialist.Before each exposure, the researcher will remind participants that, if they feel too overwhelmed during the exposure, they should remove the virtual reality head-mounted display even if they have not completed the full exposure and use the coping mechanisms that they prepared with the exposure therapy specialist. (If the participant stops the exposure early and uses a coping mechanism, the researcher will make a note of this. Postsession Subjective Units of Distress Scale (SUDS) scores will be recorded regardless.)If the participant scores >70 on any of the SUDS tests after completing the exposure, whether they ended the exposure early or not, they will be instructed by the research member on the video call to use the coping mechanisms. (The remaining SUDS scores will still be recorded.)

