Although individuals will not be excluded from the study if they have been taking benzodiazepines for longer than 12 weeks before starting phase 3, they will be asked to avoid taking them before the exposure session (only if possible and if it does not interrupt their antiseizure medication schedule). This is because benzodiazepines have immediate effects and may therefore artificially lower participants’ SUDS scores [35]. A complicating factor in this regard is that some people with epilepsy are prescribed drugs such as benzodiazepines as a rescue medication and may therefore use them to stop or prevent seizures [34,36]. In clinical practice, it is possible that the patient may take a benzodiazepine before, during, or after performing an exposure solely out of fear that they will have a seizure (and not necessarily because they are actually about to have a seizure). In this case, the patient would be actively avoiding the anxiety that is associated with the exposure. By using avoidance, the exposure’s usefulness is nullified because the patient is shielded from feelings of fear. They also momentarily lose the opportunity to learn that they are capable of handling these feelings of anxiety.

Other phase 3 exclusion criteria include individuals who have tonic-clonic seizures more than once a month, individuals who have functional seizures, individuals who cannot speak or understand English, individuals with open wounds on their face, and individuals with cervical conditions or injuries that would make it unsafe for them to use an HMD.

We will not be excluding individuals with memory deficits, as memory issues are common in people with epilepsy [37]. It is not a concern that memory difficulties will prevent participants from using the VR device properly as they will always be on a video call with a member of the research team who can guide the participant in using the VR headset as necessary.

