##### Exposure Session Protocol (T1)

###### Overview

The VR-ET intervention will consist of an exposure session every day for up to 14 days over a one-on-one video call with a researcher. During each exposure session, the participant will be seated in a chair at their home. Exposures will be performed for approximately 5 minutes, which is lower than the recommended 10-minute threshold for mitigating motion sickness [42]. Each day that the participant performs an exposure, they will complete assessments: SUDS 3 times; the Fast Motion Sickness Scale; and, although not a formal assessment, participants will be asked about the frequency in which they used coping mechanisms during the exposure session and in the 10-minute period afterward (Textbox 5).

Assessments at T1.

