#### Phase 3 Data Analysis

As both quantitative and qualitative data will be collected in phase 3, a mixed methods approach will be used. Quantitative statistical analyses will be performed using the MiniTAB statistical package [46] and SPSS software (version 27.0; IBM Corp) [47]. To investigate the normal data distributions of the dependent variables, ranges of skewness and kurtosis will be determined. The Kolmogorov-Smirnov and the Shapiro-Wilk tests will also be performed to evaluate statistical significance (mean, 95% CI) and normality of the distributions. In addition, Cronbach *α* will be performed for each self-report questionnaire’s subscales. To explore sociodemographic features, frequencies, means, and standard deviations will be calculated.

To explore the effects of VR-ET, data collected at T0 and T2 will be compared. Clinically significant effects of the intervention will be investigated using the Jacobson-Truax method, based on the measures’ clinical cut-offs (Table 2). Moreover, SUDS scores (before the exposure, immediately after the exposure, and 10 minutes after the exposure) collected every day of T1 will be compared with each other. Participants’ SUDS scores that are recorded immediately after the exposure may be lower than their anticipatory anxiety levels, and if so, this may encourage the participant to do the next exposure. We will also consider our study to be successful if participants’ SUDS scores remain high in the first postexposure SUDS test but decrease at the 10-minute postexposure SUDS test. However, the study may still be deemed successful with unchanging SUDS scores if participants have reduced anxiety and engage in fewer safety-seeking behaviors after completing VR-ET, as based on T2 findings.

Using thematic analysis, qualitative responses to assessments and interviews will be assessed by the research team and then reported as frequencies using the procedure outlined by Braun and Clarke [48]. The constant comparison method will be used to analyze the responses to the open-ended questions asked at T0 and T2 [49].

**Table 2 table2:** Clinically significant scoring for the phase 3 assessments.

		Items	Range	Scores	Citation

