We acknowledge that it may not be feasible in clinical practice for therapists to have daily communication with their clients or patients. However, we are designing the intervention this way purposefully for the pilot study to maximize safety in case of a seizure or concerning psychological distress, such as a panic attack. In addition, as discussed with a clinical neuropsychologist, it will maximize the chances of therapeutic success if participants are in communication with someone, such as a therapist or researcher, while doing the exposures to help them form a behavioral commitment. Because this is a pilot study, it aligns more with the purpose of the research to maximize the chances of therapeutic success rather than to assess the feasibility of the proposed intervention within a professional setting. However, the ability to implement self-guided sessions in a controlled and safe virtual environment is an advantage of VR therapy. Therefore, future studies should investigate participants’ adherence to VR-ET and its efficacy when they perform the exposures daily without a researcher or therapist present.

Another limitation is that while we ask participants to avoid taking a benzodiazepine before performing the exposure and after their exposure until their anxiety settles, we cannot enforce this request because benzodiazepines may be used to treat seizures [34]. As previously discussed, taking a benzodiazepine can limit the effectiveness of the ET. It may be worthwhile to conduct future clinical trials in a safe and well-monitored environment, such as a hospital epilepsy monitoring unit, where participants are restricted from taking a benzodiazepine as much as possible. In this scenario, the participants would be in a safe environment in case they were to have a seizure and potential confounding effects would be reduced.

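### The 10-minute SUDS fall counted as success cannot be separated from the coping exercises that staff instruct in the same interval when SUDS exceeds 70

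*Protocol article*

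**What the plan says.** - **Success rule.** Phase 3 Data Analysis regards the study as successful if "SUDS scores remain high in the first postexposure SUDS test but decrease at the 10-minute postexposure SUDS test". Textbox 5 gives the purpose of that pair of readings: to see whether anxiety declines in the minutes after a session.
- **Coping rule.** Textbox 2, Coping mechanisms: "If the participant scores >70 on any of the SUDS tests after completing the exposure", and regardless of whether the exposure was cut short, "they will be instructed by the research member on the video call to use the coping mechanisms". The techniques are mindfulness, self-compassion and a meditative exercise. Later SUDS readings are kept.
- **The authors' own distinction.** The text leading into Textbox 2 notes that exposure therapy ordinarily lets anxiety fade unaided, and presents coping as a precaution for this population.
- **Recording.** Textbox 5 asks about coping after each of the two post-exposure SUDS readings, so that it can be related to efficacy. Textbox 2 has staff note early stopping with coping.
- **Benzodiazepines.** Phase 3 Exclusions says that "benzodiazepines have immediate effects and may therefore artificially lower" SUDS scores, and of longer-term users that "they will be asked to avoid taking them before the exposure session", where possible. Limitations says participants are asked to "avoid taking a benzodiazepine before performing the exposure and after their exposure until their anxiety settles", and that this cannot be enforced. In the T1 Overview, each day "they will complete assessments: SUDS 3 times; the Fast Motion Sickness Scale", plus the coping question. Medication appears in the T0 background questionnaire.

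**The concern.** The rule looks for sessions that start high and then "decrease at the 10-minute postexposure SUDS test". When the first post-exposure score is above 70, a second anxiety-lowering step is instructed before the next reading. A fall could then reflect habituation to the scene, the coping exercise, or both, and the rule credits it to VR-ET either way.

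The pilot is meant to yield effect sizes and lessons for a larger trial (Study Overview and Objectives). A SUDS success signal that mixes two interventions would carry into that planning.

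**Working it through.** The protocol gives no figure for this contrast, so there is nothing to reproduce. The check sets out the order of events and then adds an illustration.

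**Order of events in one session**
1. Anticipatory SUDS, before the headset goes on.
2. Exposure of about 5 minutes. The participant may remove the headset early and use coping.
3. Immediate SUDS. If it is above 70, coping is instructed.
4. SUDS at 10 minutes.

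The success contrast is step 3 minus step 4. An immediate score above 70 places instructed coping inside that contrast. A 10-minute score above 70 also triggers coping, but after the last reading, so it does not affect that session's contrast.

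**Why recording coping does not solve it.** By rule, every session with an immediate score above 70 is a session with instructed coping. If the rule is followed, there are no uninstructed sessions above 70 to compare with. Any model relating coping to the fall would have to extrapolate from sessions at or below 70, using 5 participants and no control group.

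**Number of sessions.** 5 × 12 = 60 expected, 5 × 14 = 70 at most. The share above 70 is not given and cannot be derived.

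**Illustration (all inputs assumed, none from the documents).** Let s be the session's true SUDS, normal with mean μ = 60, 70 or 80 and SD 12. Immediate reading: a = s + e₁. Ten-minute reading: b = s + e₂ − c if a > 70, otherwise b = s + e₂. The noise SD σ is 5 or 10, the coping effect c is 0, 5, 10 or 20 points, and scores are limited to 0-100. There is no natural decline. Ranges are over μ and σ, from 400,000 simulated sessions per setting.

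| Coping effect c | Mean fall when a > 70 | Share of those sessions that fall |
|---|---|---|
| 0 | 0.7-7.9 | 52-73% |
| 5 | 5.4-12.9 | 70-86% |
| 10 | 10.3-17.9 | 82-97% |
| 20 | 20.3-27.9 | 95-100% |

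Check of one cell (c = 0, μ = 70, σ = 10). The expected fall is σ²/√(144 + σ²) × φ(0)/(1 − Φ(0)) = 100/√244 × 0.798 = 6.40 × 0.798 = 5.1, which agrees with the simulated 5.1.

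Two readings follow. The rule can be met with no habituation at all. And even with c = 0, sessions above 70 fall more often than the others (52-73% against 27-46%), simply because a high first reading tends to be followed by a lower one. A raw difference between sessions with and without coping is therefore not an estimate of what coping does.

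**The case against.** The case on the other side has real weight:

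- **The rule is narrower than the problem suggests.** Phase 3 Data Analysis does not define high. Sessions that are high but at or below 70 trigger no instruction. This stands: the overlap is certain only above 70.
- **Coping is already recorded**, at both post-exposure points and for the purpose of relating it to efficacy; a full plan could stratify on it. This stands in part. The data exist, but the success rule as printed ignores them, and a stratified analysis still faces a trigger defined by the score itself.
- **Little hangs on it.** This is an uncontrolled feasibility pilot of five people. Efficacy is left to later randomised trials, and the study can succeed on T2 findings with unchanged SUDS. This stands and limits the consequence.
- **The benzodiazepine confounding is disclosed**, and a condensed article's list of daily items does not prove that use goes unrecorded. This stands, so the point is secondary. The two descriptions of the request differ in scope rather than being flatly incompatible.

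Some stronger readings are tempting but unsupported. A reader might infer that coping produces the fall; the documents show only that the two cannot be told apart. A reader might infer that every distortion favours benefit; a benzodiazepine taken before exposure could lower all three readings and shrink the fall. A reader might put a figure such as 20-50% on the sessions affected; nothing anchors it. Participants have mild or moderate anxiety and start at the easiest scene.

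**Conclusion.** The concern holds in a limited form. In any session with an immediate SUDS above 70, the fall to 10 minutes mixes exposure with instructed coping, and the stated rule credits it as success without distinction. With five participants, no control group and a trigger set by the score itself, relating coping use to efficacy cannot separate them.

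The conclusion itself rests only on stated text. Its size cannot be fixed: somewhere between none and all of the 60 to 70 sessions, depending on an unknown share above 70. The simulated percentages show that the rule can be met without habituation; they do not predict this trial.

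The benzodiazepine point is conditional on what the full protocol records. The difference between Phase 3 Exclusions (before the session) and Limitations (before and after) needs reconciling because the later period can include the 10-minute reading. No view is taken on which scope is right.

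**What to change.** 1. Leave the safety instruction unchanged.
2. Flag each session for any coping use, instructed or self-initiated, and for early headset removal.
3. Report the immediate-to-10-minute change separately for flagged and unflagged sessions. Do not count coping-assisted falls as success or as habituation.
4. State that unflagged sessions are a less distressed subset, and that the comparison between the two groups is descriptive. The split removes neither the pull of high first readings towards the average nor the relief that comes when the scene ends.
5. Give more weight to the across-day comparison within each exposure level, which Textbox 5 already plans. Use anticipatory SUDS, and immediate SUDS with the same flags, since coping during the exposure or after early removal can precede the immediate reading.
6. If the full protocol does not already do so, add one item to each daily call: benzodiazepine taken that day (yes/no, with time), and flag those sessions.
7. Reconcile the two descriptions of the benzodiazepine request.

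The cost is small. The coping and early-stopping data are already collected, so this needs an analysis flag, a revised sentence in the success rule and at most one extra question per call. The downside is that fewer sessions, and calmer ones, then contribute to the within-session contrast.

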**Additional strategies**
If the participant’s anticipatory anxiety SUDS score (ie, the SUDS score that the participant records before performing the exposure) is >70 on the first day of beginning a new exposure level (eg, level 2), participants will still be encouraged to attempt the new level if their 10-minute postexposure SUDS score the previous day for the lower level (level 1) was <70.Even though we are excluding individuals who experience panic attacks, there is a risk that participants may panic before, during, or after the exposure. Therefore, members of the research team will be trained by a clinical neuropsychologist on how to identify when someone is having a panic attack and reach out to an on-call health professional.

###### Assessments

At baseline, the participant will also complete several assessments (Table 1 and Textbox 3), specifically the background questionnaire (Textbox 4); proposed diagnostic protocol for epilepsy-specific anxiety disorders [1]; Epilepsy Anxiety Survey Instrument (EASI); Perceived Stress Scale (PSS); and Virtual Reality Induced Symptoms and Effects (VRISE) assessment.

Assessments at T0.
**Background questionnaire**
This questionnaire was created by the authors of this paper to be conducted at the baseline interview (Textbox 4). Its main purpose is to collect phase 3 participants’ demographic information and information about their history with anxiety and epilepsy.
**Epilepsy Anxiety Survey Instrument (EASI) [39]**
The EASI is validated for assessing epilepsy-related anxiety features and severity. Note that by using the EASI, we are simultaneously using the brief Epilepsy Anxiety Survey Instrument (brEASI) [39]. The brEASI is a validated screening tool for anxiety disorders in people with epilepsy and is made up of 8 items that are already asked in the EASI. The brEASI is based on the fifth edition of the Diagnostic and Statistical Manual of Mental Disorders [40].
**Perceived Stress Scale**
The Perceived Stress Scale assesses how an individual perceives their own levels of stress.
**Proposed diagnostic protocol for epilepsy-specific anxiety disorders [1]**
Hingray et al [1] suggested a diagnostic enquiry for 4 proposed anxiety disorders specific to epilepsy: anticipatory seizure anxiety, seizure phobia, epileptic social phobia, and epileptic panic disorder. They also suggested an assessment for symptom severity of each of these disorders and an evaluation of avoidance behaviors.Note: On the basis of responses to the assessment by Hingray et al [1], individuals who appear to have epileptic panic disorder according to a clinical neuropsychologist will be excluded from the study.
**Virtual Reality Induced Symptoms and Effects (VRISE) assessment [41]**
The VRISE assessment is one of the 4 domains included in the Virtual Reality Neuroscience Questionnaire and evaluates the intensity of motion sickness. The 3 other domains included in the Virtual Reality Neuroscience Questionnaire (user experience, game mechanics, and in-game assistance) are not relevant to our study. A lower score on the VRISE assessment suggests greater motion sickness.Note: Participants who score less than 25 on the VRISE assessment after virtual reality training during T0 will be withdrawn from the study.

Overview of the questions to be asked in the Background Questionnaire (T0).DemographicsContact information of the participant and their emergency contactYear of birthSex assigned at birth and genderAddress that the participant will be doing the video calls fromTechnology usePrevious experience with virtual reality (if any)Comfort level on a scale of 1-10 with computers, smart phones, video call technology (specifically Zoom), virtual reality headsetsLow visionRecent eye surgeryEpilepsyType(s) of seizuresDate of epilepsy diagnosisSensory triggersEpilepsy safety protocol that should be set in place in case the participant were to have a seizure during the video callAnxietyPresence of anxiety as a side effect from any antiseizure medications currently takenAnxiety disorder diagnoses. Participants will be asked to list any anxiety disorders that they were diagnosed with and the dates of diagnosesHistory of experiencing preictal or postictal anxietyPrevious or current cognitive behavioral therapy (CBT). *If yes*:Date the CBT program beganDate the CBT program was completed (or the expected completion date)The helpfulness of the CBT programIf the CBT program is focused on anxiety. *If yes*, if it involved targeting epilepsy-related anxietyIf the CBT included exposure therapyIf the participant has previously undergone or if they are currently undergoing any exposure therapy. *If yes*, they will be asked similar questions as 4D (i-iv)Medical marijuana and medication use: (As this question and others in the study may be sensitive and yet important for evaluating the impact of the intervention, all outcome measures will be prefaced with an explanation of the importance of answering honestly and to the best of participants’ abilities, as well as a reminder that participation is voluntary and that questions may be skipped without repercussion.)Current antiseizure medication(s)Current medical marijuana useCurrent antidepressants or medications to treat anxiety

